## **9.4. Time to treatment failure**

Time to treatment failure is defined as the time from either (i) randomization (if patients have not yet commenced treatment) or (ii) commencement of therapy (if patients are randomized during the first cycle of imatinib) to treatment discontinuation for any reason, including disease progression, treatment toxicity, patient preference, or death.

## **9.5. Adverse Events (worst grade according to NCI CTCAE v4.03)**

The NCI Common Terminology Criteria for Adverse Events version 4 (NCI CTCAE v4.03) will be used to classify and grade the intensity of adverse events after each treatment cycle.

## **9.6. Overall survival**

Overall survival is defined as the interval from either (i) randomization (if patients have not yet commenced treatment) or (ii) commencement of therapy (if patients are randomized during the first cycle of imatinib) to date of death from any cause, or the date of last known follow-up alive.

## **9.7. Rate of patients having macroscopically complete removal of all residual disease by surgery**

This is defined as the rate of patients who proceed to surgery with the aim of resecting all remaining macroscopic disease.

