### Statistical considerations

This is a non-comparative randomized phase II design of 60 evaluable patients allocated 2:1 (38 in the alternating group and 22 in the control), The primary outcome is the objective tumour response rate by 9 months. Based on accrual of 38 evaluable patients in the alternating group, the table below, based on the charts of Mehta and Cain, give the minimum number of responses needed to be observed to be consistent with different response rate.

|                     | True response rate (%) |      |      |      |
|---------------------|------------------------|------|------|------|
|                     | 30                     | 40   | 50   | 60   |
| Number of responses | ≥ 7                    | ≥ 10 | ≥ 13 | ≥ 17 |

These limits are based on 95% lower confidence intervals for the respective response rates.

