| Tertiary and correlative objectives | 
To explore the relationship between study endpoints and:
 

▪ Change in PET imaging during washout period of regorafenib and imatinib (in subset of participants at

                                                                                                                                                                                                                                      |

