# ALT GIST

selected centres)

- Imatinib plasma levels in Arm A and imatinib and regorafenib plasma levels in Arm B.
- Circulating biomarkers as prognostic and/or predictive markers including but not limited to:
  - Circulating serum/plasma growth factor and cytokine levels (multiplex assay)
  - KIT/PDGFRA mutations in circulating blood DNA ('liquid biopsy')
  - DNA load
- Tumour tissue biomarkers including, but not limited to, proteins relating to KIT and PDGFR signalling and angiogenesis.
- Rate of patients having macroscopically complete removal of all residual disease by surgery

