# ALT GIST

This combination of imatinib, regorafenib and intervening washout periods will constitute 1 cycle of study treatment (imatinib plus washout period 28 days in total; regorafenib plus washout period 28 days in total; cycle duration 8 weeks (56 days) in total). See diagram below.

It is recommended that regorafenib should be taken orally at the same time each day (preferably after breakfast) and the tablets should be swallowed whole with water after a light low fat meal. The prescribed dose of imatinib should be taken orally, with a meal and a large glass of water to minimise the risk of gastrointestinal disturbances

Missed or vomited tablets cannot be compensated for by treatment at a later date and/or time.

[figure not shown]

Even in participants with a complete response, treatment will continue until progressive disease (PD) or prohibitive adverse events are documented. Participants who cease treatment after receiving at least 2 years of therapy from the time of commencing treatment will not be considered to have failed treatment for toxicity reasons. Surgery will be permitted for participants whose cancer becomes operable during trial treatment at the discretion of the treating team, and participants will be able to continue on study treatment and will continue to be followed for progression free survival post operatively. For patients undergoing surgery, regorafenib should be ceased at least 2 weeks prior to surgery, and recommenced on the basis of clinical judgement. During this period, imatinib could be administered until surgery and for the first 2 weeks after surgery regardless of the study Arm allocation,

Treatment after progression will be according to clinician preference and local institutional guidelines. Crossover from either arm to single agent regorafenib will not be permitted as part of the study.

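### Section 9.7 names an exploratory endpoint as complete surgical removal achieved but defines it as surgery undertaken with that aim, so the reported rate can exceed the one its title promises (minor)

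*Protocol*

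**What the plan says.** The endpoint appears in the protocol in three places under the same name: the exploratory objectives of the synopsis, the objectives table in section 3, and the heading of section 9.7. The name is "Rate of patients having macroscopically complete removal of all residual disease by surgery". In section 3 it falls under "Tertiary and correlative objectives".

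The operational definition, in the single sentence beneath the 9.7 heading, is "the rate of patients who proceed to surgery with the aim of resecting all remaining macroscopic disease". It does not mention the result of the operation, and it states no denominator.

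Section 7.1 describes how patients come to surgery: "Surgery will be permitted for participants whose cancer becomes operable during trial treatment at the discretion of the treating team". It sets no criterion for completeness of resection.

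**The concern.** The title describes something that has happened to the patient: no macroscopic disease is left. The definition describes something the team set out to do. The two come apart for any patient who is operated on with that aim and is found unresectable, or is left with gross disease. Such a patient meets the definition and does not meet the title.

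A report that follows 9.7 faithfully would give a rate of attempts under the name of a rate of complete removals. A reader would take the figure as describing what surgery achieved, and no other listed endpoint could correct that impression. Section 9.1 stops the assessment of best response at the date of surgery, so 9.7 is the only listed endpoint concerned with the result of an operation.

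The trial enrols patients whose disease is unresectable at entry (section 5.2), so an incomplete resection cannot be ruled out. The protocol does not say how often to expect one.

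**Working it through.** **Is there a figure to reproduce?** No. The protocol gives no expected rate, threshold, sample size or power for this endpoint. The check is a comparison of texts, followed by simple algebra.

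**Name against definition.**

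| Place in the protocol | What is counted |
|---|---|
| Synopsis, exploratory objectives | Removal achieved |
| Section 3, tertiary list | Removal achieved |
| Section 9.7, heading | Removal achieved |
| Section 9.7, body (the only definition) | Surgery undertaken with the aim of removal |

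**Does another section repair it?**

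- Section 7.1 leaves surgery to the treating team once disease becomes operable. It does not address the result.
- Section 9.1 restricts best response to the period before surgery.
- Section 10.1 mentions surgery for complete resection only in the list of events not reported as SAEs.
- Section 13.2 says that all randomised patients are analysed. It does not mention this endpoint.

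None of them requires complete removal to be achieved or confirmed before a patient is counted.

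**Direction and size.** Let s be the number of patients in an arm operated on with this aim, f the share of them in whom removal is macroscopically complete, and N the denominator.

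- Rate as defined: s / N
- Rate as named: s × f / N
- Ratio of the two: 1 / f

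Because f cannot exceed 1, the defined rate is never below the named rate. They are equal only when f = 1. The ratio depends on neither s nor N. With assumed values of f: 1/1.0 = 1.0; 1/0.75 = 1.33; 1/0.5 = 2.0.

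**Illustration.** N = 38 is taken from the planned "60 evaluable patients allocated 2:1 (38 in the alternating group and 22 in the control" (synopsis, statistical considerations). Both s and f are assumptions.

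| s (assumed) | As defined, s/38 | As named, f = 0.75 | As named, f = 0.50 |
|---|---|---|---|
| 4 | 4/38 = 10.5% | 3/38 = 7.9% | 2/38 = 5.3% |
| 6 | 6/38 = 15.8% | 4.5/38 = 11.8% | 3/38 = 7.9% |
| 10 | 10/38 = 26.3% | 7.5/38 = 19.7% | 5/38 = 13.2% |

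The half-patients are expected values. The 38 are evaluable patients. With all randomised patients as denominator, the percentages would shift slightly and the ratio would not.

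**The case against.** The strongest reply concerns weight. The item is last in an exploratory list, under a stem about relationships with the study endpoints. Section 13 attaches no threshold, interim look or named analysis to it. The trial is non-comparative, and section 13.1 calls the measured activity mainly descriptive. In absolute terms the gap is likely to be a few patients. All of this stands and sets the severity.

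A second reply is that the mismatch could be settled the other way, by keeping the definition and changing the name. The protocol does not show which meaning was intended, so this also stands, and renaming is an acceptable minimum. The drawback is that no listed endpoint would then record whether surgery removed the disease.

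Three stronger readings are tempting, and the documents do not support them.

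- *The rate is certain to be inflated.* The defined rate is at least the achieved rate. It is higher only if some operation of this kind fails, and the protocol gives no figure for that. Nor does the protocol label these patients successes; the impression comes from the title.
- *Open-label conduct makes the definition biased, and the change would cure this.* Surgery is discretionary, so knowledge of the arm could influence who is operated on. A patient must still be selected for surgery before removal can be achieved, so the same exposure exists under either definition. It is not a reason for this change.
- *The efficacy result is affected.* Section 9.1 cuts off response at surgery, so 9.7 cannot enter the primary endpoint.

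It might also be said that the statistical analysis plan can settle the matter. That plan is not at hand. The protocol has, however, already fixed a definition: an analysis plan that follows it inherits the mismatch, and one that does not departs from the protocol.

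**Conclusion.** The point holds as an internal inconsistency in the definition of an exploratory endpoint. The name promises complete removal achieved, the definition counts surgery undertaken with that aim, and no other section reconciles them. That the defined rate cannot be below the named one follows from the definitions and needs no assumption. The size of the gap does: the factor is 1/f, which is 1.0 to 2.0 for an assumed f between 1.0 and 0.5. The documents support no particular value in that range. The primary endpoint, the sample size and any decision rule are unaffected. The severity is minor.

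**What to change.** In section 9.7, define the numerator as patients in whom macroscopically complete removal of residual disease is documented in the operative or pathology report. State the denominator as all patients randomised to the arm, which agrees with section 13.2. Report the proportion who went to surgery with that aim as a separate descriptive line, so that attempts and results can both be read.

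If the steering committee prefers to keep the intent-based definition, the minimum is to rename the endpoint in the synopsis, section 3 and the 9.7 heading so that it describes surgery undertaken with that aim.

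The preferred change costs one sentence and one CRF item for the resection result, if that is not already collected (the CRFs are not among the documents). The reported rate may be lower. Nothing changes in who is treated or operated on.

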## **9.8. Change in PET imaging during washout period of regorafenib and imatinib in those taking part in the PET substudy**

The PET substudy aims to primarily evaluate the change in PET response during washout periods for regorafenib and imatinib. PET scans will be performed in a subgroup of participants enrolled to alternating treatment (Arm B) at selected centres. These patients will be further randomised to have PET scans either during the imatinib washout period, or during the regorafenib washout period. At these selected centres, PET scans will be conducted in addition to regular imaging studies. In the substudy, PET will be carried out on 2 occasions in each group in Cycle 2 at the earliest, or in a subsequent cycle (at the first opportunity after a complete cycle of treatment without dose modification is given). For those randomised to PET scans during the imatinib washout period, a PET scan will be performed immediately following the last dose of imatinib (or up to 2 days prior) and before the first regorafenib dose (or up to 2 days prior). For those randomised to PET scans during the regorafenib washout period, a PET scan will be performed immediately following the last regorafenib dose (or up to 2 days prior) and on the first day of the subsequent imatinib cycle prior to the first dose of imatinib (or up to 2 days prior). The change between the PET standardised uptake values (SUV) of the scan performed at

# ALT GIST

the commencement of the drug washout period and the PET SUV of the scan performed at the conclusion of the drug washout period will be assessed.

## 9.9. Biomarkers

This will include investigations of how regorafenib and imatinib may work in people with GIST, biological mechanisms of action as well as studies that may help to understand the pathogenic course of this cancer and related diseases.

Planned tissue biomarker analyses may include but are not limited to: *KIT*/PDGFRA mutation analysis and other proteins relating to PDGFR signalling.

Planned analysis of blood collected for research may include but not be limited to:

- circulating serum/plasma growth factor and cytokine levels (multiplex assay)
- imatinib plasma levels and in Arm B regorafenib plasma
- circulating tumour cells and
- *KIT*/PDGFRA mutations in circulating blood DNA
- circulating DNA load

Since the identification of new biomarkers correlating with disease activity and the efficacy or safety of treatment are rapidly evolving, the definitive list of biomarkers remains to be determined.

## 10. SAFETY REPORTING

### 10.1. Definitions

An ADVERSE EVENT (AE) is any untoward medical occurrence in a patient or clinical investigational subject administered a pharmaceutical product and which does not necessarily have a causal relationship with this treatment. An AE can therefore be any unfavourable or unintended sign (including an abnormal laboratory finding), symptom, or disease temporally associated with the use of a medicinal investigational product, whether or not considered related to the medicinal product (see below).

Adverse events include the following:

- All suspected adverse drug or device reactions
- All reactions from drug or device – overdose, abuse, withdrawal, sensitivity, toxicity or failure of expected pharmacological action (if appropriate)
- Apparently unrelated illnesses, including the worsening (severity, frequency) of pre-existing illnesses
- Injury or accidents.
- Abnormalities in physiological testing or physical examination that require clinical intervention or further investigation (beyond ordering a repeat examination)
- Laboratory abnormalities that require clinical intervention or further investigation (beyond ordering a laboratory test).

Any untoward event that occurs after the protocol-specified reporting period which the Investigator believes may be related to the drug or device.

A SERIOUS ADVERSE EVENT (SAE) is any untoward medical occurrence that at any dose:

- results in death,

## ALT GIST

- is life-threatening (i.e. the subject is at risk of death at the time of the event),
- requires inpatient hospitalisation or prolongation of existing hospitalisation,
- results in persistent or significant disability or incapacity,
- is a congenital anomaly/birth defect,
- other important medical events which, in the opinion of the investigator, are likely to become serious if untreated, or as defined in the protocol

### NOTES:

- (i) The term “life-threatening” in the definition of “serious” refers to an event in which the patient was at risk of death at the time of the event; it does not refer to an event which hypothetically might have caused death if it were more severe.
- (ii) Important medical events which may not be immediately life-threatening or result in death or hospitalization but which may jeopardize the patient or may require intervention to prevent one of the listed outcomes in the definition above should also be considered serious.

A SUSPECTED UNEXPECTED SERIOUS ADVERSE REACTION (SUSAR) is an SAE that is related to the drug or device and is unexpected (i.e. not listed in the investigator brochure or approved Product Information; or is not listed at the specificity or severity that has been observed; or is not consistent with the risk information described in the Subject Information Sheet and Informed Consent Form or elsewhere in the protocol. (FDA, Safety Reporting Requirements for INDs and BA/BE Studies, draft guidance, September 2010)).

An event is causally related if there is a reasonable possibility that the drugs, imatinib or regorafenib caused the AEs, i.e. there is evidence to suggest a causal relationship between the drug and the event.

For the purposes of this study, the following adverse events are not reported as SAEs:

- Hospitalisations related to disease progression
- Hospitalisations for management of pain related to disease
- Any elective surgery not related to cancer treatment
- Surgery for complete resection of residual disease
- Deaths related to disease progression
- Elective hospitalisation to simplify study procedures

### **10.2. Reporting of Serious Adverse Events (including SUSARs)**

The investigator is responsible for reporting all Serious Adverse Events (including SUSARs) occurring during the study to the NHMRC Clinical Trial Centre (CTC) within 1 working day of the investigator becoming aware of the event using the SAE form. All SAEs must be reported from the first dose of study treatment up to 30 days from the end of study intervention.

SAE reports should be reported to the CTC as per the procedure documented in the Study Manual. The investigator must notify their local HREC as required.

The CTC will provide SUSAR reports and SAE line listings to Investigators for submission to Human Research Ethics Committees (HRECs) as required.

For AGITG sites, the CTC will be responsible for providing reports to the Lead HREC as required.

# ALT GIST

The local study sponsor in each country/region will submit 'reportable safety events' to the local regulatory authorities (e.g. TGA in Australia, Medsafe in NZ etc.).

The following information will be recorded for each Serious Adverse Event:

- Event description including classification according to NCI CTCAE 4.03
- Severity / Worst Grade
- Attribution to study intervention
- Expectedness (listed in IB/product information),
- Action taken with study intervention
- Type of SAE (e.g. hospitalisation)
- Outcome of SAE including end date if recovered

## **10.3. Pregnancy**

In the event of a pregnancy occurring during the course of the study, the subject must be withdrawn from study drug immediately. Pregnancies occurring up to 6 months after the completion of the study drug must also be reported to the investigator. The investigator should counsel the patient; discuss the risks of continuing with the pregnancy and the possible effects on the foetus.

The local co-ordinating centre must be notified within 1 working day using the SAE form and the subject followed during the entire course of the pregnancy and postpartum period. Parental and neonatal outcomes must be recorded even if they are completely normal.

Pregnancy occurring in the partner of a patient participating in the study and up to 90 days after the completion of the test drug should also be reported to the investigator and the regional co-ordinating centre. The partner should be counselled and followed as described above.

## **11. CENTRAL REVIEW AND BIOSPECIMEN COLLECTION**

### **11.1. Central Biospecimen Collection**

Formalin-fixed paraffin-embedded (FFPE) diagnostic tumour tissue is required from all participants and will be collected for:

- pathology quality control and
- translational research (including potential future translational research relevant to this study).

The tissue will be from archival tumour material – no additional biopsy of the participant is required. Representative FFPE tissue will be collected by sites and sent to a central laboratory for analysis.

Refer to the Biological Sampling Handbook for the details of collection, processing and shipping procedures.

Blood for research will be collected from consenting participants at multiple time points and will be processed for blood components including, but not limited to serum and plasma. Processed samples will then be sent to a central laboratory for analysis. Refer to the Biological Sampling Handbook for the details of collection, processing and shipping procedures.

### **11.2. Central Imaging Collection**

Central review of CT reports will occur retrospectively and will be used for final endpoint classification for the study. A subset of CT scans may be collected on CD/DVD so these can be reviewed centrally.

Refer to the Study Manual for collection requirements

# ALT GIST

## 12. TREATMENT INFORMATION

### 12.1. *Description of Study Products*

The regorafenib 40 mg tablet is coated, not divisible, grey-orange-red, oval (length 16 mm, width 7 mm, thickness 4.9-5.6 mm) and 472 mg each in total weight. The packaging configuration is 30 tablets and a 3g desiccant capsule per bottle of regorafenib 40 mg.

Tablets are in an immediate-release dosage form with rapid dissolution characteristics under in vitro test conditions.

The regorafenib 40 mg tablet contains regorafenib and the inactive excipients microcrystalline cellulose, croscarmellose sodium, magnesium stearate, povidone, colloidal anhydrous silica, polyvinyl alcohol-part hydrolyzed, talc, titanium dioxide E171 (color index 77891), macrogol/PEG 3350, lecithin (soy), iron oxide yellow E172 (color index 77491), and iron oxide red E172.

Regorafenib tablets will be packaged separately in high-density polyethylene (HDPE) bottles with a white child-resistant closure and induction seal. Each bottle includes a desiccant. The bottles will have a label affixed containing study identification, quantity of tablets, and other details as required by local regulations. Once the drug has been received, it must be kept in a secure, dry location at a temperature not above 25 °C (77 °F).

Imatinib is manufactured as 100mg and 400mg tablets packaged in polyethylene bottles. Once the drug has been received, it must be kept in a secure, dry location at a temperature not above 30 °C.

The tablets contain imatinib, and the excipients microcrystalline cellulose, crospovidone, hypromellose, anhydrous colloidal silica, magnesium stearate, iron oxide yellow CI 77492, iron oxide red CI 77491, macrogol 4000, and talc.

